In addition at the time of the physician visit (after the self-collection), the physician will obtain 2 “pseudo self-sample” specimens (prior to placement of a speculum). These 2 samples will be kept as “dry brush samples” by placing them in plastic bags and analyzed  $\leq 7$  days and  $> 6$  wks, respectively. (45)

As mentioned above, the major problem with primary HPV testing is specificity, since most of the women testing positive will have non-neoplastic HPV infections that will spontaneously clear. To address this issue we have previously investigated primary HPV screening with a mRNA assay. (46) In addition we have explored the use of 16/18 genotyping as well as multiple other HPV types for secondary triage after primary screening using both the Cervista assay and MALDI-TOF MS. (47,48) This current trial will provide the opportunity to expand that work applied to self-collection, the Cobas assay (tests for 16 and 18 separately), and SeqHPV with separate gene sequencing for 14 HPV High-risk types.

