#### *Statistical Methods*

The primary endpoints of our study will be the sensitivity and specificity of the hrHPV tests for cervical intraepithelial neoplasia (CIN) 3 or cancer (CIN 3+). The secondary endpoints will be the sensitivity and specificity of the hrHPV tests for CIN 2+.

Our estimates of the difference in sensitivity for CIN 3+ and specificity for CIN 3+ that may be detected are based on the prevalence of hrHPV and prevalence of CIN 3+ (the primary endpoint) or CIN 2+ (the secondary endpoint) in the population studied. Our estimates of the prevalence of hrHPV and CIN 3+ are likely more accurate than in many studies as we can use the data from SHENCCAST II (17) as a guide. In SHENCCAST II (17), we screened populations similar to four of our study sites; and our fifth site (Inner Mongolia) has known hrHPV rates and resulting pre-invasive/invasive cervical cancer considerably higher than any sites in SHENCCAST II. Adding the site in Inner Mongolia should compensate for the age difference of 25-59 years (SHENCCAST II) vs. 30-59 years for the current trial (CHIMUST).

As in SHENCCAST II, sensitivities and specificities will be calculated for each hrHPV tests. Logistic regression analysis will be used to generate odds ratios and 95 % CI for factors that may be associated with test results by sampling device.

Sample size calculations to compare the sensitivity and specificity of hrHPV tests are based on the prevalence of hrHPV and the prevalence of the endpoint (CIN 3+ or CIN 2+) in the population. In SHENCCAST II, the prevalence of hrHPV measured in vaginal self-collected or endocervical practitioner-collected samples and tested for hrHPV by MALDI-TOF or Cervista assays was between 11.1% and 14.8%. The prevalence of the primary endpoint of CIN 3+ in SHENCCAST II

was 1.6% (141/8,556) while that of the secondary endpoint of CIN 2+ was 2.7% (227/8,556). The major results from SHENCCAST II are reproduced in Table 1 below. The SeqHPV assay being used in this trial, was trained and tested on SHENCCAST II specimens and showed results similar to MALDI-TOF. (19)

**Table 1: Comparison of the sensitivity and specificity for  $\geq$ CIN 3 of vaginal self-collected and physician collected specimens (endocervical) assayed for HR-HPV by Cervista and MALDI-TOF.**

(95% confidence intervals and the actual patient numbers are in parentheses).

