McNemars p-values for the comparison of the sensitivity of self-collected MALDI-TOF to physician collected Cervista is 1.0. McNemars p-value for the comparison for the specificities is  $p < 0.0001$

| SPECIMEN/HR-HPV TEST        | SENSITIVITY FOR <math>\geq</math>CIN 3 (%) (C.I.)(n) | SPECIFICITY FOR <math>\geq</math>CIN 3 (%) (C.I.)(n) |
|------------------------------------|-------------------------------------------------------------|-------------------------------------------------------------|
| Vaginal self-collected / Cervista  | 70.9% (62.7-78.3) (100/141)                          | 86.1% (85.3-86.8) (7248/8415)                        |
| Endocervical / Cervista            | 95.0% (90.0-98.0) (134/141)                          | 90.3% (89.6-90.9) (7598/8415)                        |
| Vaginal self-collected / MALDI-TOF | 94.3% (89.1-97.5) (133/141)                          | 87.5% (86.8-88.2) (7370/8415)                        |
| Endocervical / MALDI-TOF           | 94.3% (89.1-97.5) (133/141)                          | 89.4% (88.7-90.0) (7526/8415)                        |

The 95% CI for the sensitivity of hrHPV in Table 1 spans about 8%, suggesting that, with a study involving 10,000 women with prevalence of hrHPV of 11.1 to 14.8% and prevalence of CIN 3+ of 1.6%, we can reliably detect a difference in sensitivity of about 8%. The 95% CI for the specificity of hrHPV in Table 1 spans only about 1.3% suggesting that we can reliably detect differences in specificity of the hrHPV test greater than 1.3%. As we have paired specimens, the difference in sensitivity for CIN 3+ that can reliably be detected is closer to 7% i.e. 94.3% (133/141) vs. 87.2% (123/141) rather than 8%.

*Primary Objective: Evaluation of the Cobas 4800 Assay, and the SeqHPV Assay for the detection of high grade pre-cancer of the uterine cervix, in population based screening samples obtained using self-collection.*

To evaluate the comparative sensitivities and specificities of the hrHPV platforms, the sensitivity and specificity of each test will be calculated using biopsy showing CIN 3+ (primary endpoint) or CIN 2+ (secondary endpoint) as the gold standards.

*Secondary objective 1: To evaluate differences in assay performance using solid (filter paper cards), dry brush, and liquid based specimen transport for the self-collected and physician collected cervico-vaginal specimens.*

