To determine which kind of sample collection media is a suitable medium for collecting and storing vaginal self-samples relative to the assay used we will calculate sensitivities for detecting CIN2+

and CIN3+ and the number of insufficient samples for hrHPV testing of the different sample collection transport systems.

*Secondary objective 2: To evaluate cytology and genotyping as secondary screens after primary hrHPV screening using Cobas and SeqHPV.*

The focus will be to explore practical algorithms that will maximize specificity for CIN 3+ with minimal loss in sensitivity for CIN 3+. Differences in sensitivity and specificity for CIN 3+ will be compared with McNemar's test when there are paired results and Chi-Square when there are independent groups. Cytology will be analysed as a triage technology with a special focus on the non-HPV 16/18 positive population. For the genotyping analysis the available types (14 HPV types) will be used from SeqHPV. Types 16/18 will be used from SeqHPV and Cobas.

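### Secondary objective 1 judges transport media on sensitivity and insufficient samples and leaves out specificity, so extra false positives would not count against a medium

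*Protocol*

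**What the plan says.** Protocol section 3.3, Statistical Methods, states the scope of secondary objective 1 broadly: "To evaluate differences in assay performance using solid (filter paper cards), dry brush, and liquid based specimen transport". The analysis text under that objective is narrower. To settle which medium is suitable for self-samples, it says "relative to the assay used we will calculate sensitivities for detecting CIN2" or worse. The same sentence then completes its list of measures: "and CIN3+ and the number of insufficient samples for hrHPV testing of the different sample collection transport systems". It lists no other measure.

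Specificity appears elsewhere in the same section:

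- Endpoints: "The primary endpoints of our study will be the sensitivity and specificity of the hrHPV tests", for CIN 3+ as primary and CIN 2+ as secondary.
- General statement: "As in SHENCCAST II, sensitivities and specificities will be calculated for each hrHPV tests".
- Primary objective: "the sensitivity and specificity of each test will be calculated using biopsy showing CIN 3+ (primary endpoint"), with CIN 2+ as the secondary standard.
- Secondary objective 2: "Differences in sensitivity and specificity for CIN 3+ will be compared with McNemar's test when there are paired results".

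Section 2 says that "the major problem with primary HPV testing is specificity". It also reports that the earlier evaluation of the POI card was judged on sensitivity and specificity together.

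**The concern.** Of the three objectives, the media comparison is the one whose analysis text drops specificity. It is also a comparison where specificity matters. If a carrier or elution step turns additional specimens positive and leaves the other results unchanged, its sensitivity stays the same or rises. The additional positives among women without disease are not insufficient samples, so they affect neither listed measure. Followed as written, the text could rate a medium with more false positives as equal or better. Each false positive is a woman recalled for colposcopy in a screening programme.

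The omitted measure is also the more precise one. By the protocol's own figures, differences of about 7 to 8 points in sensitivity are detectable, against 1.3 points in specificity. Media may therefore look alike on sensitivity through imprecision alone, while a real difference in specificity would be visible if it were examined.

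**Working it through.** **Inputs, all from section 3.3 (Table 1 and the text around it).** CIN 3+ in the earlier trial: 141 of 8,556, leaving 8,415 women without CIN 3+. MALDI-TOF, self-collected: 133/141 positive among cases and 7,370/8,415 negative among non-cases. MALDI-TOF, endocervical: 133/141 and 7,526/8,415. Planned size: 10,000 women.

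**Step 1: reproduce Table 1** (proportions with exact 95% confidence intervals).

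| Row | Measure | Stated | Recomputed |
|---|---|---|---|
| Both MALDI-TOF rows | Sensitivity, 133/141 | 94.3% (89.1-97.5) | 94.3% (89.1-97.5) |
| Self-collected | Specificity, 7,370/8,415 | 87.5% (86.8-88.2) | 87.6% (86.9-88.3) |
| Endocervical | Specificity, 7,526/8,415 | 89.4% (88.7-90.0) | 89.4% (88.8-90.1) |

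Agreement is within 0.1 point.

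**Step 2: compare on sensitivity.** 133/141 − 133/141 = 0. On this measure the two specimens are equal.

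**Step 3: compare on false positives.**

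- Self-collected: 8,415 − 7,370 = 1,045.
- Endocervical: 8,415 − 7,526 = 889.
- Difference: 1,045 − 889 = 156, and 156/8,415 = 1.9 points.
- Positive predictive value: 133/(133 + 1,045) = 11.3% against 133/(133 + 889) = 13.0%.

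**Step 4: scale to this trial.** Expected CIN 3+ cases: 10,000 × 141/8,556 ≈ 165, so about 9,835 non-cases. False positives: 9,835 × 1,045/8,415 ≈ 1,221 against 9,835 × 889/8,415 ≈ 1,039, a difference of about 182. The gap of 1.9 points is above the 1.3 points that the protocol calls reliably detectable.

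**Step 5: would a paired test see it?** Table 1 does not give the discordant counts, so I took the whole possible range with a net difference of 156. The exact McNemar p-value is about 2 × 10⁻⁴⁷ at 156 versus 0, 5 × 10⁻⁷ at 556 versus 400, and 0.0004 at the extreme of 1,045 versus 889. It is at most 0.0004 throughout.

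**Step 6: are the data there?** Under the assay list in section 3.1, SeqHPV is run on every card, and both assays on every self-collected liquid sample. Women positive on any specimen are recalled for colposcopy. A woman whose card and liquid SeqHPV results disagree is positive on one of them and so is referred by design. A paired comparison of false positives is therefore feasible for that contrast. It does not extend unchanged to the others: Cobas on the card is a nested case-control analysis, dry brushes are taken only in Inner Mongolia, and the dry-brush Sample B analysis is nested.

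**The case against.** The best reply is that specificity is already planned. It is an endpoint, and the general statement promises it for each hrHPV test on the pattern of the earlier trial, whose Table 1 gives every specimen and assay combination its own row with both measures. On that pattern, card/SeqHPV and liquid/SeqHPV would each receive a specificity, and detailed tables may sit in a statistical analysis plan that is not shown. The text for secondary objective 1 also sets no threshold or ranking; it says only what will be calculated.

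Part of this stands. Specificity by medium could well be tabulated, and the documents do not show that it would go unreported. The absence of a formal decision rule is also correct. But the general statement is made per test and is not linked to the choice of medium. The protocol itself names the measures for that choice and omits specificity, whereas the other two objectives include it. This is a choice the protocol makes, and not detail deferred to a later document.

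Stronger readings are tempting but unsupported:

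- **Size.** A reader might take the widest specificity gap among the three Table 1 rows with similar sensitivity, endocervical Cervista against self-collected MALDI-TOF. This gives (7,598 − 7,370)/8,415 × 9,835 ≈ 266 extra false positives. That pair differs in both assay and collection site. Even the same-assay pair used above differs in collection site. Neither estimates an effect of the medium.
- **Mechanism.** A reader might infer carry-over from the manual punching of cards. The protocol describes the punching but reports no contamination.
- **Denominator.** A reader might infer that sensitivity will be computed among adequate samples only, which would flatter a medium that fails more often. The text gives no denominator.

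**Conclusion.** The concern holds as a fault in the measures named for secondary objective 1. As written, the basis for judging a medium suitable omits specificity, and a medium with more false positives could be rated equal or better. The protocol's own data show two specimens tied on sensitivity and 1.9 points apart on specificity, about 182 false positives per 10,000 women. That figure illustrates what the named measures cannot see. It assumes the earlier trial's CIN 3+ prevalence and specificities, and it is not a forecast for card, liquid or dry brush. How much any medium adds is unknown from the documents.

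The full-cohort denominator of about 9,835 non-cases applies to SeqHPV on card versus self-collected liquid. The dry-brush and nested comparisons rest on fewer women. The primary objective is not affected. The change is worth making before analysis because it is cheap and the main comparison needs no new data.

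**What to change.** Amend secondary objective 1 in section 3.3 as follows:

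1. Within each assay, compare media on both sensitivity and specificity, for CIN2+ and CIN3+, with paired differences, 95% confidence intervals and McNemar's test (already planned for secondary objective 2). State that both measures are weighed in judging suitability.
2. Make SeqHPV on card versus self-collected liquid the full-cohort comparison. Limit dry-brush comparisons to Inner Mongolia. For the nested card-Cobas and Sample B analyses, use sampling weights or restrict the comparison to the sampled subset, because unweighted specificity there depends on how the controls were chosen.
3. Keep reporting insufficient samples by medium. If a sensitivity analysis counts them as not detected, apply it to sensitivity only. Applied to specificity, it would turn failed samples in women without disease into true negatives and favour the medium that fails more often.

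The cost is a few sentences and some extra tables, plus the weighting for the nested assays.

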#### **1.1 Secondary Objectives:**

- 1) To evaluate differences in assay performance using solid (filter paper cards), dry brush, and liquid based specimen transport for the self-collected and physician collected cervico-vaginal specimens.
- 2) To evaluate cytology and genotyping as secondary screens after primary HPV screening using Cobas 4800, and SeqHPV.

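### McNemar's test cannot show a minimal loss of sensitivity when a triage rule is compared with its own primary screen, because all discordance runs one way

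*Protocol*

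**What the plan says.** Protocol section 1.1 sets the second secondary objective: "To evaluate cytology and genotyping as secondary screens after primary HPV screening using Cobas 4800, and SeqHPV". Section 3.3 (Statistical Methods, Secondary objective 2) gives the aim, "The focus will be to explore practical algorithms that will maximize specificity for CIN 3+ with minimal loss in sensitivity for CIN 3", where the endpoint is CIN 3 or worse. It then names the tests: "Differences in sensitivity and specificity for CIN 3+ will be compared with McNemar's test when there are paired results". For unpaired data it provides a chi-square test. On cytology it adds: "Cytology will be analysed as a triage technology with a special focus on the non-HPV 16/18 positive population".

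The text does not say what a triage rule is to be compared with. It gives no figure for a minimal loss, no significance level and no version of McNemar's test. It also does not say that a non-significant result counts as a minimal loss.

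**The concern.** A loss of sensitivity needs a reference. For a second step applied after a primary hrHPV screen, the natural reference is that screen. Both results come from the same women, so by the protocol's own wording the comparison is paired and McNemar's test applies.

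A rule of the form screen-positive and then triage-positive cannot be positive in a woman whose primary screen is negative. Against its own screen, sensitivity can only fall or stay equal, and specificity can only rise or stay equal. One discordant cell is zero by construction. A test of equality is a poor tool here, because the question is how much is lost and not whether the direction is down. If non-significance were read as a minimal loss, a rule could be recommended on the strength of few cases. That would be easiest in the non-16/18 group, where the protocol puts its emphasis for cytology.

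**Working it through.** **Inputs.**
- CIN 3+ prevalence for planning is 1.6% (section 3.3, earlier trial: "was 1.6% (141/8,556) while that of the secondary endpoint of CIN 2+ was 2.7% (227/8,556"). With the planned 10,000 women this gives 160 cases.
- Sensitivity of the primary screen is 94.3% (133/141, Table 1, MALDI-TOF). Screen-detected cases: 0.943 × 160 ≈ 151.
- Two-sided 0.05 is assumed; the protocol states no level but uses 95% intervals.
- The number of CIN 3+ cases among non-16/18 positives is not in the documents. I assume 40 to 100.

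**Reproducing the protocol's own figures.** Exact (Clopper-Pearson) intervals give 89.1–97.5% for 133/141 and 90.0–98.0% for 134/141, as printed in Table 1. The protocol reports a McNemar p of 1.0 for that pair. With a net difference of one case, the exact and continuity-corrected tests give p = 1.0 for every possible split of discordant pairs (1/0 to 8/7). The uncorrected test gives 0.32 to 0.80. The reported value therefore fits the exact or corrected version only.

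**Nested comparison.** Let k be the CIN 3+ cases that are screen-positive but triage-negative. The opposite cell is 0.
- Exact two-sided: p = 2 × 0.5^k
- Continuity-corrected: chi-square (1 df) = (k − 1)²/k
- Uncorrected: chi-square (1 df) = k

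| Cases lost, k | Exact p | Corrected p | Uncorrected p |
|---|---|---|---|
| 3 | 0.25 | 0.248 | 0.083 |
| 4 | 0.125 | 0.134 | 0.046 |
| 5 | 0.0625 | 0.074 | 0.025 |
| 6 | 0.031 | 0.041 | 0.014 |

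The largest non-significant loss is five cases (exact or corrected) or three (uncorrected). The total number of cases appears in none of the formulas.

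**What five lost cases mean.** The last column is the chance, P(X ≤ 5) for X binomial(n, 0.07), that a true 7% loss yields a non-significant exact test.

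| Screen-detected cases, n | 5/n | Exact 95% CI | True 7% loss not flagged |
|---|---|---|---|
| 151 (all) | 3.3% | 1.1–7.6% | 4% |
| 100 (assumed) | 5.0% | 1.6–11.3% | 29% |
| 80 (assumed) | 6.3% | 2.1–14.0% | 51% |
| 60 (assumed) | 8.3% | 2.8–18.4% | 76% |
| 40 (assumed) | 12.5% | 4.2–26.8% | 94% |

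**Specificity.** The same arithmetic applies to women without CIN 3+. Six spared women already give exact p = 0.031. In Table 1, self-collected MALDI-TOF had 8,415 − 7,370 = 1,045 false positives, so any triage rule of practical use will give a significant gain. That p-value carries little information either.

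**The case against.** The strongest reply is that the protocol nowhere says the comparison is with the primary screen. The same paragraph covers cytology, 14-type genotyping from SeqHPV and 16/18 genotyping from both assays. Rules compared with each other, or across assays or specimens, are not nested in general, and McNemar's test suits them. This stands, and it limits the point to the nested case.

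A reader might infer that the plan passes any rule losing up to five cases. The documents do not support that. The aim is to explore, section 3.1 reserves cytology for future research and not for patient care, and no pass rule is written. The missing numerical limit may also sit in an analysis plan that is not shown, and alone it would be no finding.

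A reader might also infer that the null hypothesis can never be true for a nested pair. That goes too far. It holds if a rule drops only women without CIN 3+, so it is a boundary null, which a single lost case refutes. That the p-value ignores the total number of cases is a property of McNemar's test in general.

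On size, five losses in the whole set are about 3 sensitivity points (5/160 = 3.1%), below the 7% that section 3.3 regards as reliably detectable, and a true 7% loss would be flagged about 96% of the time. The subgroup figures rest on assumed counts and are losses within the subgroup. If 16/18-positive women stay positive under the rule, the same five cases remain about 3% overall. Finally, sensitivities are to be calculated as in the earlier trial, whose table shows counts and intervals, so losses would probably be visible.

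What remains is that the test named for paired results does not answer the stated question when a rule is set against its own screen.

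**Conclusion.** The point holds for one comparison: a screen-positive-and-triage-positive rule against its own primary screen. There a non-significant McNemar p does not establish that the loss is minimal. Up to five lost CIN 3+ cases would be non-significant with the exact or corrected test, or three with the uncorrected test. This assumes two-sided 0.05; the exact or corrected version is inferred from the reported p = 1.0.

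For the full set the effect is modest: 3.3% of about 151 cases, upper limit 7.6%. It grows as the case count falls, and for non-16/18 positives that count is unknown: 5.0% to 12.5% over the assumed 100 to 40 cases. The risk is that non-significance is read as minimal loss; the protocol does not itself prescribe that reading. For an exploratory secondary objective this is an inexpensive improvement, and the primary analysis is untouched.

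**What to change.** In section 3.3, Secondary objective 2, treat the two kinds of comparison separately.

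- **Triage rule against its own primary screen:** replace McNemar's test with the proportion of screen-detected CIN 3+ cases lost, overall and among non-16/18 positives, with an exact 95% CI. Report beside it the proportion of recalls avoided. Judge whether the loss is minimal by the upper confidence limit, against a limit fixed before analysis.
- **Paired comparisons that are not nested** (rule against rule, assay against assay, specimen against specimen): keep McNemar's test as written.

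To show what a limit would imply, for illustration only: with 151 screen-detected cases, an upper limit below 5%, 7% or 10% allows at most 2, 4 or 7 losses. With 60 cases, even zero losses leave an upper limit of 6.0%.

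The cost is a change of wording, with no new data. The downside is that, with few cases, some rules will be reported as inconclusive.

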- 5) At ALL sites a physician will then place a vaginal speculum so as to directly-collect an endo-cervical sample from each of the participants. The sample is placed in 20ml ThinPrep® PreservCyt® (TCT) Solution (Hologic); ONLY in Inner Mongolia, prior to placement of the vaginal speculum, the physicians will obtain 2 “pseudo self-samples” which are allowed to dry, then placed into plastic bags for testing at ≤7days and >6wks respectively using a) Roche-Cobas 4800 and b) BGI-SeqHPV test.

The direct samples will be assayed using a) Roche –Cobas and b) BGI-SeqHPV.

Cytology using the Hologic I2 imager systems (computer assisted cytology) will used for future research not for patient care in the current study. The primary goal will be to explore secondary triage for the non-16/18, HPV positive women.

**POI Card Management Protocol** – Each card will be manually punched 4 times and placed in a single well in a 96-well plate. Then they are all washed once using 100 microliters sterile water. The water is carefully removed with a sterile fine-tip pipette. The DNA elution is performed in 50 microliters of sterile water at 56°C for 30 min immediately followed by 95°C for 15 min. in a heating block. The 96-well plate containing DNA elution and pieces of card are centrifuged at 4000 rpm for 3 min and the eluted DNA is transferred into a new 96-well plate. (Any required storage will be at -80°C for further use). When performing the assays 5ul of DNA will be used in each well of the 96 well plates for PCR for SeqHPV. 10ul will be used for a nested case control study using Cobas. (It should be noted that this is the standard volume used for SeqHPV, and it has been thoroughly tested and demonstrated to be optimal with > 99% adequate specimens. It was determined in our prior study that 10ul optimized the Cobas Assay when using the POI card.)

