### **3.3 Data Management and Statistical Methods:**

#### *Data Management*

A strict system of data management will be utilized. All participating women will be assigned a study ID number upon entry into the study. Only the Principal Investigator and Project Coordinators will have access to the complete files matching personal identifiers to the confidential study ID numbers. Laboratory samples and results are identified only by confidential code numbers with no

available personal identifiers. Laboratory information that could in any way be linked to a particular study participant by name or personal identifier will not be released except to provide that patient with needed medical care and appropriate follow-up care. All reports, publications and scientific presentations of the findings from the study will be absent of any personal identifiers, and therefore presented without the identities of individual participants.

Samples are tracked and the study questionnaire and laboratory data will be entered onto the study data forms at the clinical sites. The forms will be copied and the original copy transferred to the data management office at Peking University Shenzhen Hospital to be dual entered into the Study Data Management System. These files will be backed up nightly. All forms will be stored in locked files by the Project Coordinator.

Data management will include quality control procedures including the employing of range checks and assessment of completeness and consistency across variables. The site specific data manager will be supervised by the study assigned epidemiologist and biostatistician. All data will be merged into one cleaned and locked database to create a final set for data analysis.

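### A triage rule found by searching this one cohort will appear to keep more CIN 3+ than it really does, unless its accuracy is corrected for the search

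*Protocol*

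**What the plan says.** Protocol section 3.3, Statistical Methods, secondary objective 2, sets an optimisation goal: "The focus will be to explore practical algorithms that will maximize specificity for CIN 3+ with minimal loss in sensitivity for CIN 3"+. The inference follows directly: "Differences in sensitivity and specificity for CIN 3+ will be compared with McNemar's test when there are paired results", with chi-square for independent groups.

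The material available to such a search is also described there. "For the genotyping analysis the available types (14 HPV types) will be used from SeqHPV"; types 16 and 18 are also available from Cobas. "Cytology will be analysed as a triage technology with a special focus on the non-HPV 16/18 positive population".

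Section 3.1 describes one cross-sectional cohort, and section 3.3, Data Management, describes one analysis set: "All data will be merged into one cleaned and locked database to create a final set for data analysis". No second sample, hold-out or resampling is mentioned. No candidate rules are listed, and no number is attached to the acceptable loss of sensitivity.

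The status of the work is clear. Section 3.1 says of cytology: "The primary goal will be to explore secondary triage for the non-16/18, HPV positive women". Section 2 reports earlier work of the same kind: "we have explored the use of 16/18 genotyping as well as multiple other HPV types for secondary triage".

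**The concern.** A rule kept because it loses few CIN 3+ in a given sample has been selected partly on chance. A genotype that happens to carry few cases among these women looks safe to leave out of referral, although its true share of CIN 3+ may be larger. If the rule's sensitivity is then computed in the same women, it is biased upward. The usual confidence interval and p-value treat the rule as though it had been fixed beforehand.

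For triage this is the unhelpful direction, because the rule would appear to miss fewer CIN 3+ than it would in new women. The number of cases is small, and the stated focus is on non-16/18 positives, where cases per type are fewest.

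**Working it through.** **1. The protocol's own precision figure.** Section 3.3 says that the 95% CI for sensitivity spans about 8%. Exact intervals agree: 133/141 gives 89.1-97.5 (8.4 points) and 134/141 gives 90.0-98.0 (7.9 points). The protocol gives no size or precision figure for the triage search.

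**2. Inputs from the protocol.**
- CIN 3+ prevalence in the earlier Shenzhen trial: "was 1.6% (141/8,556) while that of the secondary endpoint of CIN 2+ was 2.7% (227/8,556"). In 10,000 women, 1.6% gives 160 cases; the unrounded 141/8,556 gives 165.
- Self-collected sensitivity of 94.3% (Table 1): 0.943 × 160 = 151 HPV-positive CIN 3+. Table 1's own count of 133 serves as a lower value.
- Specificity of 87.5% (Table 1): 0.125 × (10,000 − 165) = 1,229 HPV-positive women without CIN 3+.

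**3. How thin the cases are.** If types 16 and 18 account for 40-70% of cases (assumption), 151 × 0.30 = 45 to 151 × 0.60 = 91 cases remain for 12 types. That is about 4 to 8 per type, before any split by cytology.

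**4. Size of the overstatement.** This was simulated. Each stratum *k* is a genotype by cytology result, with true case share *p_k*, observed case count *c_k* and non-case count *n_k*. Types 16 and 18 are always referred. The search drops the set *S* of other strata that removes the most non-cases, subject to Σ*c_k* ≤ floor(*L* × *N*), where *L* is the allowed loss and *N* the number of cases.

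- Apparent retained sensitivity = 1 − Σ*c_k*/*N* over *S*
- True retained sensitivity = 1 − Σ*p_k* over *S*
- Overstatement = apparent − true

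Assumptions not in the protocol: HPV 16 in 35-50% and HPV 18 in 8% of cases (17% and 6% of non-cases); the other types either declining in frequency or equal; cytology positive in 80% of cases and 15% of non-cases.

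Worked scenario: *N* = 151, *L* = 5%, HPV 16 in 50% of cases, other types declining. The limit is floor(7.55) = 7 lost cases, and 144/151 = 95.4%. Average apparent sensitivity is 95.4% and average true sensitivity 91.9%, an overstatement of 3.5 points. The unadjusted 95% interval covers the true value in about 80% of runs.

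| How the rule arises | Overstatement of retained sensitivity |
|---|---|
| Free search, 133-151 cases, *L* = 3-10% | 2.7 to 4.5 points |
| Same, 300 cases | 1.3 to 2.3 points |
| Simpler search on genotype alone, 151 cases | 2.5 points (96.3% vs 93.8%) |
| Best of five fixed rules, true sensitivity 89-97% | 1.1 to 1.2 points |
| Best of five rules all truly at 92%, *L* = 5% | about 3.8 points, but a rule qualifies in only about a quarter of studies |
| One rule fixed in advance | 0 |

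In the free search, the share of false positives removed is overstated by 1 point or less. The problem is almost entirely in sensitivity. Further runs with other assumed mixes put the free search at roughly 3 to 5 points, so the overall range is stated as about 2.5 to 5.

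**5. Does the remedy work?** In the worked scenario, 10-fold cross-validation with the search repeated in each fold gives 91.6%, against a true 91.9%. Only the cases were folded, so this checks the correction of sensitivity. Splitting the cohort in half is also unbiased for its own rule (89.1% vs 89.2%) but leaves only about 75 cases for testing.

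**6. What McNemar's test adds.** Women positive after triage are a subset of those positive at the primary screen, so against that screen all discordance among cases runs one way. With *b* lost cases the exact p is 2 × 0.5^*b*: 0.125 for 4, 0.0625 for 5, 0.031 for 6 and 0.016 for 7. Losing 5 of 151 (3.3%) cannot reach p < 0.05, so a non-significant result does not show that the loss is minimal. A search that uses up its allowance loses floor(0.03 × 151) = 4 cases at a 3% limit (p = 0.125) and 7 at a 5% limit (p = 0.016). The p-value then mostly reflects the limit chosen.

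**The case against.** The strongest reply is that the protocol commits to very little here. The objective is secondary and twice described as exploration, and section 3.1 reserves cytology for future research rather than patient care in this study. Candidate rules, a tolerated loss and internal validation are normal content for an analysis plan, which is not shown. The rules that the text comes closest to naming, 16/18 genotyping and cytology in the remaining positives, could be fixed in advance, and earlier work could supply others. For such rules the bias is zero or small.

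Most of this stands and limits the point. A reader might infer that the reported sensitivity is bound to be overstated, or that a recommended rule will miss more cases than claimed. The documents support neither: they do not say that one rule will be chosen, validated or recommended, they set no retention target, and the genotype mix behind the figures is assumed. Nor is McNemar's test the cause. Selection is, and the specificity comparison with the primary screen rests on hundreds of one-way discordant pairs that selection could hardly overturn.

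What the reply does not remove is that the stated goal is an optimisation, the stated tests suit rules fixed beforehand, and only one cohort is described. Calling the work exploratory does not correct the estimate for a rule found that way.

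**Conclusion.** The point holds conditionally. If a triage rule is chosen by searching genotypes and cytology in this cohort and its apparent accuracy is reported uncorrected, retained CIN 3+ sensitivity will be about 2.5 to 5 points too high for a free search with about 151 HPV-positive cases. For a typical short list it is about 1 point, and for a single prespecified rule nothing. The unadjusted interval and p-value would not reflect the selection. For scale, the protocol regards about 7 points as the smallest paired difference in sensitivity that it can reliably detect.

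The direction follows from selection itself. The size rests on the assumed genotype mix, the cytology performance and an allowed loss of 3-10%. The primary endpoints are unaffected. This is an inexpensive improvement to a secondary objective, not a flaw in the trial's main comparison.

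**What to change.** Before analysis:
- Fix a short list of rules, for example 16/18 alone, and 16/18 plus cytology for the other types.
- State numerically the loss of CIN 3+ sensitivity that will be tolerated.
- Keep McNemar's test for these rules. Judge loss by the estimate and its interval against the tolerated limit, not by a non-significant p-value.

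For any rule found by search:
- Report sensitivity and specificity from repeated 10-fold cross-validation or a bootstrap optimism correction, with the whole search repeated in every fold or resample.
- Label the rule hypothesis-generating.

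Leave-one-site-out results may be shown only as a check on transportability. Section 3.3 expects considerably higher disease rates in Inner Mongolia than at the earlier trial's sites, so that method would mix optimism with differences between sites.

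The cost is some programming and a reported sensitivity a few points lower for searched rules. No new data are needed.
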